# *Sahaj Samadhi* meditation vs a Health Enhancement Program in improving late-life depression severity and executive function: study protocol for a two-site, randomized controlled trial

**DOI:** 10.1186/s13063-019-3682-z

**Published:** 2019-10-24

**Keywords:** Late-life depression, Treatment-resistant late-life depression, Executive functioning, *Sahaj Samadhi* meditation, Health Enhancement Program, Randomized controlled trial

## Abstract

**Background:**

Recent estimates suggest an 11% prevalence of current late-life depression (LLD) and a lifetime prevalence of 16–20%. LLD leads to cognitive disturbance as well as a nearly two to three times increased risk of dementia. We conducted a recent randomized controlled trial (RCT) which demonstrated that *Sahaj Samadhi* meditation (SSM), an easy-to-implement, meditation-based augmentation strategy, led to higher rates of symptom remission when compared to treatment as usual (40.0 vs 16.3%; odds ratio, 3.36; 95% CI 1.06–10.64; *p* = 0.040). Here we present a protocol describing a two-site, blinded, RCT, comparing an SSM arm to an active-control arm – a Health Enhancement Program (HEP) intervention – in their ability to reduce depressive symptoms and improve executive functioning, among several other exploratory outcomes.

**Methods/design:**

One hundred and ninety-two (*n* = 192) participants with LLD will be recruited at two sites (London, ON, Canada, and Montreal, QC, Canada). Participants will undergo stratified randomization with regards to site and the presence of treatment-resistant-LLD (TR-LLD) or not, to either SSM or HEP. We will assess change in (1) depression severity using the Hamilton Depression Rating Scale (HAM-D), (2) executive functioning, and (3) other exploratory physiological and mood-based measures, at baseline (0 weeks), post intervention (12 weeks), and 26 weeks after baseline. Raters, clinicians, and care providers will be blinded to group allocation while participants will be blinded to the study hypotheses.

**Discussion:**

This study should more definitively assess whether SSM can be used as an augmentation strategy in routine clinical care for patients suffering from LLD and TR-LLD. If the effects of SSM are significantly better than HEP, it will offer support for the routine use of this intervention to manage LLD/TR-LLD and comorbid declines in executive dysfunction. The results of this study could also inform whether SSM can improve/prevent cognitive decline in LLD.

**Trial registration:**

ClinicalTrials.gov, ID: NCT03564041. Registered on 20 June 2018.

## Background

### Late-life depression

The older adult population is growing worldwide with those aged 60 years and older to comprise over 22% of the global demography by 2050 [1]. In some regions of the world, such as North America, this shift is predicted to occur within the next 10 years [2–4]. An estimated 15% of individuals within this age group are currently living with a mental illness [5]. Late-life depression (LLD), specifically, has been found to have a current prevalence of 11% [6] and a lifetime prevalence of 16–20% [7, 8]. Direct healthcare costs incurred through treatment of LLD patients are approximately 33% higher than for their non-depressed counterparts [9] and have been reported to be as high as CAD$5 billion per year in Canada, alone [10]. Indirect costs (e.g., informal caregiving; suicide) have been reported to be as high as CAD$1.8 billion [11]. These considerable costs could be reduced by the successful treatment of LLD and its treatment-resistant variant (TR-LLD).

The standard treatment for LLD is the use of antidepressants, such as selective serotonin-reuptake inhibitors (SSRIs), and/or psychotherapy. These current treatments, however, have significant limitations. Patients are frequently not able to tolerate adequate doses and, as such, there is often poor compliance with pharmaceutical-based treatment plans. In addition, the monoamine theory of depression does not seem to address other psychosocial circumstances which have been implicated in the precipitation and maintenance of depression [7]. Given the above, it is no surprise that treatment resistance (TR) is prevalent in up to 60% of patients with LLD [12]. Also, it has also been shown that as many as 30% of patients with LLD discontinue their antidepressants within 6 months of initiation due to drug-related adverse effects [12].

Alternatives to pharmaceutical management of LLD include various psychotherapy interventions. Such evidence-based interventions include problem-solving therapy, interpersonal therapy, and cognitive behavioral therapy [12, 13]. Despite the efficacy of these therapies there is often a lack of trained professionals, inability to access this care, or, in patients where therapy is available, a wait time of up to 18 months [14]. The prevalence of LLD, associated costs, lack of response to pharmacotherapies, and difficulty accessing conventional psychotherapies and pharmacotherapy consultations raises the need to find novel, cost-effective, and scalable interventions for this important mental health disorder.

### Depression, dementia, and other related risks/illnesses

A depressive episode has been found to nearly double a person’s chance of developing dementia as shown by previous meta-analyses [15, 16]. Studies also have demonstrated that 30–50% of LLD patients show impairments in cognitive functioning [17]. Additionally, patients with LLD report impairments in memory, attention, information processing, and executive functioning [16, 18, 19]. Executive functioning, in particular, has been found to be directly associated with LLD [18]. This executive dysfunction persists and significantly interferes with treatment responsiveness in LLD and has been implicated as one of the most important markers for conversion to dementia [20]. In the United States alone, the healthcare costs associated with managing dementia have been calculated to be as high as USD$215 billion per year [21]. Even though there are effective care models established for dementia, its irreversible nature highlights the importance of investigating the preventive potential of various non-pharmacological interventions such as exercise- and meditation-based therapies.

LLD and TR-LLD are also associated with a multitude of health comorbidities. These include: stress [22], anxiety, suicidal ideation [23], lower quality of life, increased medical comorbidity, and higher mortality rates compared to age-matched controls [14]. Attempts have been made to understand the neurobiology of LLD and TR-LLD and, so far, a host of brain and other systems have been implicated including cortisol dysregulation [24], cardiovascular autonomic impairment [25], gait disturbances [26–28], increased presence of inflammatory markers [20, 29, 30], sleep disturbances [31, 32], as well as structural and functional brain changes [33–35]. It is hence important to assess changes, if any, in these pathophysiological pathways. It is possible that any new treatment strategy for LLD and/or TR-LLD could lead to reversal of these changes.

### *Sahaj Samadhi* meditation

Recent research has shown benefits of some mind-body (e.g., yoga, *tai chi*, mindfulness) interventions in reducing depressive symptoms across the age span [36–40]. *Sahaj Samadhi* meditation (SSM) is a less-investigated meditation intervention which differs from others as it lets the practitioner attain a deep state of relaxation aided by the use of a personalized mantra, which is to be used only when needed, during the meditation practice. It does not require focus on one’s thoughts or environment, on mindfulness or on frequently repeating a mantra as in focus-based meditation techniques.

The authors conducted a recent randomized controlled trial (RCT) on SSM in LLD compared to a treatment-as-usual (TAU) arm. It was observed that those in the SSM arm had a significantly greater decrease in depressive symptoms compared to the TAU arm (mean point-change difference − 2.66; 95% CI − 5.05 to − 0.26; *p* = 0.030), with 40% of SSM participants entering remission compared to 16.3% in the TAU arm (odds ratio of 3.36; 95% CI 1.06 to 10.64; *p* = 0.040) [37]. There were no reported side effects associated with SSM. Additionally, participants’ qualitative feedback included remarks stating that SSM is easily learned and can be practiced as part of a daily routine. The observed practical benefits of SSM included relative affordability, the ability to be taught in a group setting, and easy transferal to community/clinical settings [37, 39]. SSM may additionally ameliorate the cognitive impairments associated with LLD and TR-LLD as other transcendental meditation techniques – practiced twice a day, 2 days per week, for 12 weeks (as in the present study) – have shown improvements in this domain [41]. Furthermore, there is some pilot data to suggest that the category of meditation to which SSM belongs, namely automatic self-transcendental meditation (ASTM), positively affects immune responses to stress [42].

For the purpose of further exploration of the beneficial effects of SSM we plan to conduct a study with the primary hypothesis that SSM, compared to an active control, will lead to a significant improvement of depressive symptoms in participants with LLD at 12 weeks and that this effect will persist at 26 weeks. We will also examine a secondary hypothesis that SSM leads to an improvement in other variables including executive function. Exploratory outcomes will be changes in anxiety, quality of life, gait, and central as well as peripheral immune function.

## Methods/Design

### Aims

The objective of this study is to compare the effects of *Sahaj Samadhi* meditation (SSM) on related psychological and biological outcomes against an active control, the Health Enhancement Program (HEP).

Primary outcome: the primary outcome measure will be change in depression scores in the SSM arm compared to HEP at 12 weeks. We will also assess the percentage of SSM participants who will meet the clinical criteria for remission compared to HEP at 12 weeks. Lastly, we will assess whether participants in the SSM arm will continue to have reduced depression scores at the 26-week follow-up.

Secondary outcome: the secondary outcome measure will be a neuropsychological battery for assessing executive function with an emphasis on planning and organization ability, at the primary endpoint of 12 weeks.

Exploratory outcomes: for a complete list of such outcomes and their associated hypotheses, please refer to Table 1.

**Table 1 Tab1:** Objectives and hypotheses

Objective		Hypothesis
Primary		
1.	Using a 12-week RCT, assess whether SSM improves depressive symptoms in LLD compared to an active-control condition; HEP	(a) In participants with LLD, SSM participants, compared to HEP controls, will have a greater reduction in depressive symptoms from baseline to 12-week follow-up, as measured by the Hamilton Rating Scale for Depression (HRSD-17) (b) Compared to HEP, a higher percentage of SSM LLD participants will meet the clinical criteria for remission, as defined by HRSD-17 scores < 8 at the 12-week follow-up
Secondary		
2.	To assess the effects of SSM on a specific executive function, i.e., organization ability in LLD	In participants with LLD, compared to HEP, SSM will be associated with better organization ability, at 12-week follow-up
Exploratory		
3.	To assess the effects of SSM on other executive function domains in LLD	In participants with LLD, compared to HEP, SSM will be associated with better executive functions, at 12-week follow-up
4.	To assess the effects of SSM on global cognition in LLD	In participants with LLD, compared to HEP, SSM will be associated with better global cognition, at 12-week follow-up
5.	Using magnetic resonance spectroscopy (MRS), assess the effects of SSM on functional connectivity measured by rs-fMRI particularly within the area implicated on the default mode network, volume increase in the bilateral hippocampi and posterior cingulate cortices and levels of glutathione (GSH)	Compared to HEP, SSM will show an increase in functional connectivity especially within the area implicated on the default mode network and also a volume increase in the bilateral hippocampi and posterior cingulate cortices and an increase in levels of GSH in key mood-regulating brain areas (ventro-medial prefrontal cortex)
6.	To investigate whether SSM intervention is associated with sustained improvements in participants’ views of disability (WHODAS 2.0), sleep (Athens Insomnia Scale), quality of life (Euro-QOL), anxiety (Generalized Anxiety Disorder GAD-7, and overall psychological well-being (Ryff’s Scales of Psychological Well-Being; SPWB 9 items) at 12-week follow-up compared to HEP	SSM will be superior to HEP at 12 weeks on all self-rated measures of disability, sleep, quality of life, anxiety, and psychological well-being
7.	To investigate the effects of SSM and HEP on mood and cognition at 26-week follow-up	SSM will continue to be superior to HEP at 26-week follow-up with regard to HRSD-17 scores and executive functioning
8.	To identify and quantify the extent of gait impairment in participants with LLD and explore the effects of SSM intervention on gait impairments at 12 weeks	SSM will be superior to HEP in improving gait measures, including stride length, gait velocity and fear of falling and risk of falling as measured by the Falls Efficacy Scale – International (FES-I) at 12-week follow-up
9.	To explore whether blood inflammation markers, circadian rhythm, and sleep quality (Acti-watch), predict treatment response with SSM	Depression and anxiety symptoms will be associated with levels of inflammatory markers. Levels of inflammatory markers will be decreased, as well as circadian rhythm and sleep quality (Acti-watch) will be improved, in the SSM participants at 12-week follow-up compared to HEP, which in turn will be associated with greater reductions in depression/anxiety scores
10.	To assess participant experience after participating in the interventions (SSM or HEP)	Using the semi-structured McGill Illness Narrative Interview, elucidate what is the participant experience participating in either SSM or HEP?
11.	To assess the extent to which participanting in SSM or HEP is associated with any change in mindfulness scores using the Five Facet Mindfulness Questionnaire (FFMQ)	Compared to HEP, SSM is associated with greater increases in FFMQ mindfulness scores. This in turn is associated with greater improvements in HRSD-17 depression scores (see main outcome section)
12.	To explore whether there are any changes in level of consciousness, at week 12, participants will fill out the self-report Phenomenology of Consciousness Inventory (PCI) after their meditation session for the SSM group or analogous activities for the HEP group	Participants practicing SSM will be in an altered state of consciousness compared to participants engaged in HEP

*HEP* Health Enhancement Program, *LLD* late-life depression*, rs-fMRI* resting state  functional magnetic resonance imaging, *RCT* randomized controlled trial, *SSM Sahaj Samadhi* meditation

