### Participants

Research participants will be 192 men and women between 60 and 85 years of age who meet the criteria for a mild or moderate major depressive episode according to a structured clinical interview using the Mini International Neuropsychiatric Interview (MINI) [43]. This will be confirmed by a score of between 10 and 22 on the Hamilton Rating Scale for Depression (HRSD-17) [44, 45].

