### Primary outcomes

The HRSD-17 scores at baseline, 12-week, and 26-week follow-up of participants assigned to SSM and HEP will be compared using linear mixed models: 2 (SSM vs HEP) × 3 (0 weeks, 12 weeks, 26 weeks). This approach will account for the clustering of observations, since both SSM and HEP will be delivered in a group setting. Next, we will evaluate whether a greater proportion of participants assigned to SSM, compared to HEP, achieve depression remission (defined as a HRSD-17 score ≤ 7 at the 12-week follow-up) using generalized linear mixed models (hypothesis 1B).

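### The remission model for hypothesis 1b names no baseline HRSD-17 term; if it is run unadjusted, the comparison is valid but gives up some power

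*Protocol article*

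**What the plan says.** Table 1 in the protocol article (Aims) places remission under the primary objective. Hypothesis (b) is that, against HEP, "a higher percentage of SSM LLD participants will meet the clinical criteria for remission, as defined by HRSD-17 scores" below 8 at week 12. The text of the same section makes change in score the primary measure and adds remission to it: "We will also assess the percentage of SSM participants who will meet the clinical criteria for remission compared to HEP at 12 weeks".

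The Primary outcomes part of the Statistical analysis section treats the two differently. For the score, "The HRSD-17 scores at baseline, 12-week, and 26-week follow-up of participants assigned to SSM and HEP will be compared using linear mixed models", in a layout of two arms by three time points. Remission, written there as 7 or less (the same rule on an integer scale), is to be analysed "at the 12-week follow-up) using generalized linear mixed models (hypothesis 1B"). No covariate is named for this model or for any other.

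The Participants section confirms eligibility by a "score of between 10 and 22 on the Hamilton Rating Scale for Depression (HRSD-17"). Recruitment and Randomization and blinding give site and treatment resistance as the only strata. Table 2 has the HRSD-17 measured in everyone at week 0. The Sample size section justifies 192 participants for the HRSD-17 score and states no power for remission.

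**The concern.** The cut-off is absolute and the entry range is wide, so two participants can face very different distances to remission. The usual way of using that information is to put baseline severity in the model.

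For the continuous score this happens without further wording, because week 0 is one of the modelled time points. That route is closed for remission. With entry at 10 or above, remission status at week 0 is the same for everyone and carries no information. Baseline severity can therefore reach hypothesis 1b only as a named covariate, and none is named. An analyst following the text literally would use baseline for part (a) of the primary objective and not for part (b).

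What is at stake is precision. A prognostic covariate raises the power of a logistic-type model. Naming it beforehand also removes a later choice between adjusted and unadjusted results.

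**Working it through.** **Distance to remission.** From the entry range and the cut-off: 10 − 7 = 3 points at one end and 22 − 7 = 15 points at the other.

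**The plan's own figure.** The pilot difference and effect size in Sample size imply an SD of 2.66 / 0.61 = 4.36. For a 2.6-point difference, n per arm = 2 × (1.96 + 0.84)² × (4.36 / 2.6)², which rounds up to 45, or 90 analysed. With 16% attrition that is 90 / 0.84, or 108 recruited, before clustering. The expected 160 completers correspond to a design effect of 160 / 90 = 1.78. From 1 + (m − 1) × ICC, this means an ICC of about 0.26 for groups of 4, 0.13 for 7 and 0.09 for 10. The article states no ICC, so 192 can be neither reproduced nor called wrong. The attrition step agrees: 160 / 0.84 = 190.5.

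**Power for remission without adjustment.** The only remission rates in the article are the pilot's 40% against 16.3%, where the comparator was treatment as usual. The difference is 0.237 and the mean rate 0.2815. With 80 per arm:

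- null SE = √(2 × 0.2815 × 0.7185 / 80) = 0.0711
- alternative SE = √((0.4 × 0.6 + 0.163 × 0.837) / 80) = 0.0686
- z = (0.237 − 1.96 × 0.0711) / 0.0686 = 1.42, so power is 92%

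With the implied design effect, the effective n is 80 / 1.78 = 45 per arm and the same formula gives 71%.

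**Gain from adjustment.** This was simulated with 3000 trials per setting, using logistic regression with a two-sided Wald test at 5%. Arm only was compared with arm plus baseline HRSD-17. Assumptions not in the article: baseline uniform over the integers 10 to 22; a latent normal week-12 score cut to give the stated remission rates; the correlation ρ between baseline and week 12; and every remission rate other than 40% and 16.3%. Clustering was approximated by using 45 per arm; no mixed model was fitted. Entries are power in %, unadjusted → adjusted.

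| n per arm | SSM vs HEP | ρ = 0 | ρ = 0.3 | ρ = 0.5 | ρ = 0.6 |
|---|---|---|---|---|---|
| 80 | 40 vs 16.3 | 92.1 → 92.3 | 92.9 → 94.0 | 93.1 → 95.9 | 92.6 → 97.3 |
| 80 | 35 vs 16.3 | 77.0 → 77.0 | 77.8 → 80.4 | 79.1 → 84.9 | 77.7 → 86.8 |
| 80 | 40 vs 25 | 53.5 → 53.7 | 53.5 → 54.9 | 54.5 → 61.0 | 52.9 → 63.8 |
| 45 | 40 vs 16.3 | 71.8 → 71.2 | 71.3 → 73.4 | 70.9 → 77.2 | 71.2 → 81.0 |
| 45 | 35 vs 16.3 | 51.6 → 50.9 | 52.2 → 53.4 | 51.3 → 58.2 | 53.2 → 62.9 |
| 45 | 40 vs 25 | 33.6 → 33.4 | 33.8 → 35.1 | 33.6 → 37.0 | 32.9 → 40.2 |

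The largest gain at ρ up to 0.3 is 80.4 − 77.8 = 2.6 points. At 0.5 to 0.6 the gains run from 95.9 − 93.1 = 2.8 to 63.8 − 52.9 = 10.9 points. The slight falls at ρ = 0 are within simulation error, which is at most √(0.25 / 3000) = 0.9 points for each power.

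A second simulation used other assumptions: baseline mean 16 and SD 3.25 truncated to 10–22, week-12 SD 5, a 2.6-point effect, remission about 43% against 24%, 80 per arm and no clustering. Power went from 71.7 to 73.7 at ρ = 0.3, from 69.7 to 77.1 at 0.5 and from 70.2 to 79.9 at 0.6. Direction and size agree.

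**The case against.** The strongest reply is that the article names no covariates for any model and says that it rests on an internal protocol that is not shown. A covariate list is commonly left to that document or to the analysis plan. This stands. A reader might infer that baseline severity has been excluded from the remission model, but silence in a condensed article does not show that. Any loss is conditional on the final model being unadjusted.

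Four further readings are tempting and also go too far.

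- If the two-by-three layout were carried over to remission, week 0 would hold no remitters and its log-odds terms would have no finite estimate. The article attaches that layout to the linear model only and ties remission to week 12.
- Chance differences in severity between the arms might be taken for bias. They are not: an unadjusted comparison of randomised arms is valid, and its standard error already covers them.
- Baseline might be thought to decide largely who remits, or to be the strongest predictor available. The article gives no correlation and ranks no predictors.
- Hypothesis 1b might be read as falling short of a promised power. None is promised for it.

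It is also fair to say that with the pilot rates and 80 per arm, power is already about 92% and adjustment adds at most 97.3 − 92.6 = 4.7 points. That setting ignores clustering. It also borrows a gap seen against treatment as usual, whereas HEP is designed to match non-specific effects, so a smaller gap is plausible.

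**Conclusion.** The point holds as a recommendation, not as an error. The stated remission model has no baseline term, and baseline severity cannot enter it by the route that the continuous model uses. Left unadjusted, the analysis remains valid but loses roughly 0 to 3 points of power at a correlation up to 0.3 and about 3 to 11 points at 0.5 to 0.6. These ranges depend on assumed correlations, HEP remission rates and clustering, and they include almost no loss. The power claimed for the HRSD-17 score is not affected by this point.

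**What to change.** State in the analysis section that the week-12 remission model contains arm, continuous baseline HRSD-17 and the treatment-group random effect. Add that the SSM − HEP difference in remission percentage will be reported, standardised over the observed baseline distribution, since hypothesis 1b concerns percentages. If the full protocol or the analysis plan already says this, a cross-reference is enough.

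No new data are needed, because the HRSD-17 is taken in everyone before randomisation. There are two small costs. The adjusted odds ratio is conditional on baseline and will not match the crude one. The standardised difference needs a standard error that respects the treatment groups, for example from a bootstrap that resamples whole groups. The wording should be fixed before any results by arm are seen.

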## Outcomes

A screening assessment will be conducted to determine a participant’s eligibility for the study. Following completion of the informed consent process, baseline assessments will be completed. Demographics collected at baseline include age, biological sex, and self-identified gender, ethnicity, height, weight, along with hip and waist circumference, as well as housing, marital, and employment status. A medication record will be collected as per participant report along with reconciliation from pharmacy records.

The following scales will be administered at the baseline assessments (a complete list of the assessments to be completed at different time points can be found in Table 2).

**Table 2 Tab2:** Primary and secondary outcome measures for all participants; weeks 0–26

Evaluations	Enrollment	Randomization and interventions’ start	Follow-ups	
	Week 0	Week 1	Week 12	Week 26
Primary outcome: depression				
HRSD-17	✓		✓	✓
Secondary outcome: executive function				
WAIS-IV–Digit Span	✓		✓	✓
D-KEFS Verbal Fluency Test	✓		✓	✓
California Verbal Learning Test-II, Short form	✓		✓	✓
Rey-Osterrieth Complex Figure–Copy Trial	✓		✓	✓
D-KEFS Color Word Test Conditions 1–3	✓		✓	✓
Exploratory and screening measures:				
To be administered by examiner:				
MINI-COG	✓			
PHQ-9	✓		✓	✓
ATHF	✓			
Mini International Neuropsychiatric Interview	✓			
CIRS-G	✓			
CGI (Severity portion only)	✓			
CGI (entire scale)			✓	✓
Athens Insomnia Scale	✓		✓	✓
MoCA (London only)	✓			✓
WAIS-IV–Test of premorbid functioning	✓			
To be completed by participant:				
FES-I (London only)	✓		✓	✓
PHQ-9	✓		✓	✓
GAD-7	✓		✓	✓
GAI	✓		✓	✓
WHO DAS 2.0	✓		✓	✓
EQ-5D-5 L	✓		✓	✓
TTO	✓		✓	✓
TSES	✓		✓	✓
PCI			✓	✓
SPWB	✓		✓	✓
FFMQ	✓		✓	✓
Likert scale			✓	
Participant-reported side effects			✓	✓
Other data collected:				
Assessment of eligibility	✓			
Informed consent	✓			
rs-fMRI/MRI/sMRI (only if enrolled in MRI sub-study)	✓		✓	
Demographics (including medications)	✓			
Changes in demographics (including medications)			✓	✓
Acti-watch^a^ (Montreal only)	✓		✓	
Gait (London only)	✓		✓	✓
Blood draw (London only)	✓		✓	

^a^this measure is administered 2 weeks prior to week 0 and 2 weeks following week 12

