#### Falls Efficacy Scale – International (FES-I)

The FES-I is a 16-item, self-rated scale used to assess fear of falling. Participants are asked about their fear of falling while doing various daily tasks (e.g., “Going up or down stairs”) and rate items on a scale of 1 (“Not concerned at all”) to 4 (“Very concerned”). Scores range from 16 to 64, with higher scores indicating greater fear of falling [73].

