#### Gait

Outcomes include mean stride length and mean gait velocity. Both stride length and gait speed will be measured using a GAITRite® portable walkway (CIR Systems Inc., Franklin, NJ, USA). This device utilizes embedded pressure sensors that electronically collect necessary information. Participants will be asked to walk along the walkway and perform various tasks in a single length of the device: (1) complete a normal walk down the walkway; (2) count backwards from 100 by 1; (3) name as many animals as possible; (4) count backwards from 100 by 7; and (5) walk as fast as possible without running down the walkway. A normal walking pace will be gathered using the device prior to the above tasks. This task will be completed at the London (ON, “Canada”) site only and will be conducted in the Brain and Gait laboratory of [name], located at the Parkwood Institute in London, ON, Canada.

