### Randomization and blinding

After baseline assessments, participants will be randomly assigned to the SSM or HEP arm of the study. Group allocation will be stratified by site (London or Montreal). Additionally, participants will be stratified to the presence of treatment resistance (TR) or not. Stratification and randomization will be conducted by an independent statistician based in London, ON. An independent member from administrative staff at the London site will receive the list of randomization and save it on a secure electronic database with access available to the principal investigator (PI) only if the code needs to be broken in an emergency. This process will ensure that group allocation remains concealed from raters, clinicians and care providers. Due to the nature of the intervention being behavioral in nature, it is not possible to blind participants to study arm assignment.

Participants will be informed by telephone of group allocation by an administrative assistant not involved in the study. Alternatively, participants will be handed a sealed envelope (prepared by the same administrative assistant) by a research assistant.

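### Exploratory hypothesis 8 assigns risk of falling to the FES-I, which the protocol defines as a fear-of-falling scale; no other scheduled measure covers falls or fall risk

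*Protocol article*

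**What the plan says.** Table 1 (protocol article, Aims) lists twelve objectives. Number 8 is exploratory. Its objective column speaks only of gait impairment. Its hypothesis column goes further and predicts superiority on stride length, gait velocity and "fear of falling and risk of falling as measured by the Falls Efficacy Scale – International (FES-I) at 12-week follow-up".

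The section on the Falls Efficacy Scale – International describes the instrument: "The FES-I is a 16-item, self-rated scale used to assess fear of falling". On item content it says: "Participants are asked about their fear of falling while doing various daily tasks". On the score it says: "Scores range from 16 to 64, with higher scores indicating greater fear of falling".

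The Gait section says: "Outcomes include mean stride length and mean gait velocity". Table 2 places the questionnaire among the participant-completed measures at weeks 0, 12 and 26, marked "FES-I (London only)".

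**The concern.** Fear of falling and risk of falling are different quantities. The first is what a person feels and reports. The second concerns the chance that the person will fall. The hypothesis treats one self-rated score as the measure of both, although the protocol's own definition covers only the first.

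At stake is what may be concluded from a favourable FES-I result. In people aged 60 to 85, less fear of falling is a statement about how they feel. A lower risk of falling is a statement about physical safety, and a reader may act on it. The hypothesis as worded would let the same result stand behind both statements. A larger sample would not cure this, because the gap lies in what is measured and not in how precisely.

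**Working it through.** The point involves no power, sample-size or error-rate figure, so the check sets the relevant sections side by side.

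1. **What the hypothesis assigns to the FES-I.** Grammatically, the phrase naming the instrument may govern both fall-related terms or only the nearer one. Risk of falling is the nearer one, so it is tied to the FES-I on either reading.

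2. **What the protocol says the FES-I measures.** The instrument's purpose, its item content and the meaning of its score are each described, and each time as fear. The range is internally consistent: 16 items × 1 = 16 at the low end and 16 items × 4 = 64 at the high end. The whole range is therefore made up of ratings of concern, and no item is described as recording a fall.

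3. **Whether another scheduled measure covers fall risk.**
   - Gait section: the named outcomes are stride length and velocity, recorded under several walking tasks. Neither is called a measure of fall risk.
   - Table 2: there is no falls count, falls diary or fall-risk instrument at any visit.
   - Toronto Side Effects Scale and the participant-reported side effects in Table 2: neither is described as recording falls, and hypothesis 8 points to neither.

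4. **Result.** Of the two fall-related quantities in hypothesis 8, fear of falling has a matching instrument. Risk of falling has only an instrument that the protocol defines as measuring something else.

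5. **Whether this is just condensation in a journal article.** It is not. The article does not leave the measure of fall risk to a fuller document. It names one, and the name conflicts with its own description of that instrument.

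6. **Whether later data collection could fill the gap.** Trial progress reports 44 enrolled by 22 July 2019: 26 completed, 7 in the intervention and 11 withdrawn (26 + 7 + 11 = 44). A falls question added after that date would have no data for the 26 completers. How many of them were at London is not stated.

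**The case against.** The strongest case on the other side is that this is loose wording in a summary table, already limited by the measure's own description. The FES-I section fixes the meaning of the score, "with higher scores indicating greater fear of falling", and a report that follows it would report fear. Where the article says what it hopes to learn (end of Background, Discussion, Conclusion), it refers to gait and physiological outcomes and never to falls. The analyses it describes cover only the primary and secondary outcomes. All of this stands, and it limits the weight of the point. It does not remove the mismatch, because Table 1 is where the hypothesis is fixed.

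Two stronger readings are tempting, and the documents support neither.

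- **That the trial will claim a lower risk of falling.** The text is a hypothesis. It shows which conclusion a favourable result would be used to support, not a claim that will be made.
- **That a mood or anxiety effect would be passed off as a fall-risk effect.** A reader might infer this because the scale is self-rated, "it is not possible to blind participants to study arm assignment", and hypothesis 6 expects anxiety to improve. That anxiety drives the FES-I is a plausible inference, but the documents do not state it. Participants are blinded to the study hypotheses, and the control programme is active and matched for time. Two anxiety scales, the PHQ-9 and instrumented gait are recorded at the same visits, so an FES-I change with improved anxiety and unchanged gait could be seen in the trial's own data. Those measures make a misreading less likely, but they do not supply a fall-risk outcome.

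One might also argue that fear of falling is an acceptable proxy for fall risk. The protocol does not make that argument, and judging it would need outside evidence. Even then, the score would have to be labelled as a proxy.

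**Conclusion.** The point holds as a definite but minor inconsistency. Hypothesis 8 names a fear-of-falling scale as the measure of fall risk, and nothing else scheduled measures falls or fall risk. A favourable FES-I difference could support a conclusion on fear of falling but none on risk of falling.

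The size is one phrase in one of twelve objectives. That objective is exploratory and rests, for this measure, on an unstated share of the planned 192 participants, those at London. The primary outcome, the secondary outcome, the sample size and the safety procedures are untouched. It should not be read as a flaw in the trial's design.

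The conclusion assumes that the article's description of the FES-I and its Table 2 are complete as to what is measured. If the full protocol schedules a falls record, hypothesis 8 should point to that record instead.

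**What to change.** Delete the words *and risk of falling* from hypothesis 8 in Table 1, and interpret the FES-I as fear of falling only. No data collection, visit or test changes. The only downside is a narrower exploratory claim.

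A question on falls since the last visit could be added at weeks 12 and 26, when participants are already asked about other changes, but the fix does not need it. It would be missing for everyone who had already completed, and whether a recalled count at two visits could support a comparison between arms would have to be considered first.
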